**Fig. 1 Fig1:**
[figure not shown]
Study design

The primary implementation outcomes will be rates of scheduling and completion of genetic counseling appointments, stratified by factors such as referral clinic and diagnosis, with cumulative nudges representing a time-varying covariate. Decisions to undergo genetic testing in a timely manner are dependent on several factors, including patient preference. Additionally, a counseling discussion can alleviate some patient concerns about testing and may be more acceptable to patients. As such, scheduling the initial genetic counseling appointment was chosen as a primary outcome in addition to appointment completion. Process outcomes will include open rates for the two patient-directed strategies and the proportion of pended orders signed by referring clinicians. We will compare the number of appointments scheduled after each sequence and across patient-level characteristics (e.g., race and ethnicity) and site.

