## Background

Breast cancer is the most common cancer for women across the world [1–3]. Approximately 300,000 new breast cancer cases were estimated in the USA for 2022, accounting for roughly one-third of new cancer diagnoses among U.S. women [4, 5]. Although less common, ovarian cancer ranks as the deadliest gynecologic cancer, accounting for about 20,000 cases and 13,000 deaths per year [4, 6, 7]. Moreover, substantial health inequities exist for both cancers. Early-stage diagnosis is critical for increasing survival rates [8, 9], but Black women tend to be diagnosed at later stages than white women [7, 10], and mortality rates for both diseases are > 30% higher for Black women as compared to white women [7, 11, 12].

In the past decade, multigene panel tests have been increasingly used to analyze several genes associated with breast and ovarian cancer [13–15]. Genetic testing can inform risk assessment, suggest interventions for risk reduction, and change options for therapy [16]. Multiple FDA approvals for PARP inhibitors for the treatment for BRCA-associated cancer, including early-stage, high-risk breast cancer [17, 18], have changed the landscape with regard to medical intervention [19]. As such, patients [20, 21] and clinicians [20, 22, 23] are generally interested in genetic testing and the National Comprehensive Cancer Network (NCCN) recommends testing for specific groups (e.g., people with personal histories of ovarian cancer) [14]. Unfortunately, there is a clear practice gap in genetic testing uptake, with only about 35% of ovarian cancer patients undergoing testing [24–27]. In assessing two large gynecology practices in our health system, we found higher rates than average of genetic testing among patients diagnosed within the last two years with early-onset breast cancer or triple-negative breast cancer. However, we found very low rates of genetic testing in individuals who were (1) diagnosed with ovarian cancer previously, or (2) had a family history of ovarian cancer or male breast cancer. Testing rates of those with a family history (rather than a personal history) of cancer were less than 15%. Moreover, substantial health inequities exist in testing rates. Eligible Black women are much less likely to be tested than their non-Hispanic white counterparts [11, 25–28], a finding replicated in the analysis of our own data, even with similar referral rates for all patients meeting our eligibility criteria.

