### Sample size, power, and statistical analysis

Based on preliminary assessments via electronic phenotyping in the EHR, we have identified a target sample of around 3000 patients (clustered within approximately 30 physicians at the two Penn Medicine sites) who may benefit from genetic testing for familial high-risk breast and ovarian cancer predisposition but have not done so. We calculated power conservatively by assuming correlations of 0 to 0.2, using PASS (Power and Sample Size, NCSS Software, Kaysville, UT). We found our sample gives us 80% power to detect at least a 5% improvement in our cumulative incidence of testing using a two-sided type 1 error rate of 5%, for planned comparisons between each stage in the sequence.

We will analyze the change in the incidence of scheduling counseling appointments across the three sequences (all time to event outcomes) using Cox regression, with variances adjusted for physician clustering. The models will contain time-varying binary predictor terms for each nudge, making adjustments for time in months, and fixed effects for site. We will control for type 1 error inflation by hierarchical testing, starting with the overall model significance, followed by the effect of each strategy. Once we have fitted the main effects model, we will test for each sequence and retain terms if significant (alpha = 5%). Variability in outcomes by sequence and moderators (particularly health equity variables) will be assessed using interaction terms within Cox regression models. We will fit an adjusted Cox regression model using the same approach described in the primary analysis. Covariates of interest available through the EHR will be added to the model, including patient-level (e.g., race), clinician-level (e.g., physician type), and practice-level (e.g., community vs. hospital-based) data.

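### The primary outcomes are described as stratified by clinic and diagnosis, but the primary Cox model has no diagnosis term, which leaves the portal contrast open to confounding if diagnosis mix differs by portal access

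*Protocol article*

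**What the plan says.** All references are to the protocol article.

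- **Study design, paragraph after Fig. 1.** Scheduling and completion rates are the primary outcomes, "stratified by factors such as referral clinic and diagnosis", and the same sentence makes the accumulating nudges a time-varying covariate.
- **Sample size, power, and statistical analysis, main model.** Scheduling is analysed "using Cox regression, with variances adjusted for physician clustering". The terms are then listed: "The models will contain time-varying binary predictor terms for each nudge, making adjustments for time in months, and fixed effects for site". Type 1 error is controlled hierarchically, with the overall model first and then each strategy, and terms are retained if significant at 5%.
- **Same section, later model.** "We will fit an adjusted Cox regression model using the same approach described in the primary analysis". Its covariates are given by example: "Covariates of interest available through the EHR will be added to the model, including patient-level (e.g., race), clinician-level" and practice-level data. Diagnosis is not among the examples.
- **Measures.** Diagnosis is collected as a potential moderator, and rates are to be evaluated within strata of the listed factors.
- **Patient nudges.** Patients found to have no portal account move directly to the text-message step.
- **Study setting, population, and duration.** Diagnosis or family history defines eligibility, so it is known for every patient at baseline.

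**The concern.** A time-varying covariate is a regression term. A sentence that joins it to stratification by clinic and diagnosis therefore reads most naturally as a description of the primary model. Of the two stratifying factors named there, clinic reappears in the model as site and diagnosis does not.

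This matters because the study is not randomized, so adjustment is its main protection against differences in patient mix. The stratified rates, the interaction terms and the adjusted model all use patient characteristics, but none of them carries the hierarchical tests of each strategy. The model that does carry them compares, at least in part, patients who had a portal account with patients who did not. The Background itself acknowledges differential portal access. If the two groups also differ in diagnosis, and diagnosis predicts scheduling, part of that difference will be read as an effect of the portal message.

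**Working it through.** **Plan's own figures.** The article gives no figure on this point: no diagnosis mix, no scheduling rate by diagnosis and no share without a portal account. Its 80% power statement does not bear on the question. It also cannot be reproduced, because the baseline incidence and the type of correlation are not stated. Everything below therefore rests on assumed inputs, shown as ranges, with no true nudge effect throughout.

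**Notation.** *s* is the share of patients in a higher-uptake diagnosis group, *h* is its hazard ratio against the rest, and *p* is the scheduling probability per step in the lower-uptake group.

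**1. Change of mix between steps (depletion).** The mean relative hazard at a step is m·h + (1 − m), where m is the share still at risk from the higher-uptake group. After each step that group is multiplied by (1 − p)^h and the rest by (1 − p).

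Example with s = 0.30, h = 2, p = 0.05:
- Step 1: 0.30 × 2 + 0.70 = 1.300.
- After two steps: 0.30 × 0.9025² = 0.2444 and 0.70 × 0.95² = 0.6318, so m = 0.2444 / 0.8762 = 0.279.
- Step 3: 0.279 × 2 + 0.721 = 1.279. Ratio of step 3 to step 1: 1.279 / 1.300 = 0.984.

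Over s = 10, 30, 50%, h = 1.5, 2, 3 and p = 2, 5, 10% (27 combinations), the ratio runs from 0.896 to 0.999. It is within 5% of 1 in 22 of the 27.

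**2. Difference of mix between contact routes.** The ratio of mean hazards, no portal to portal, is (s₀h + 1 − s₀) / (s₁h + 1 − s₁), where s₁ is the share among account holders and s₀ among the rest.

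| s₁ (portal) | s₀ (no portal) | h | No portal / portal | Portal / no portal |
|---|---|---|---|---|
| 30% | 30% | 2 | 1.00 | 1.00 |
| 30% | 20% | 2 | 1.2 / 1.3 = 0.92 | 1.08 |
| 50% | 20% | 2 | 1.2 / 1.5 = 0.80 | 1.25 |
| 50% | 20% | 3 | 1.4 / 2.0 = 0.70 | 1.43 |
| 20% | 50% | 3 | 2.0 / 1.4 = 1.43 | 0.70 |

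The last row shows that the direction reverses if the mix is reversed.

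**3. Fitted model.** This was a piecewise-exponential simulation with 3000 patients, 20% without a portal account (assumed), three-week steps, 12 weeks of follow-up, a weekly hazard of 0.02 in the lower-uptake group and 60 replicates. Nudge indicators were cumulative. Site and physician clustering were left out. Hazard ratios, all truly 1:

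| s₁ / s₀ / h | Portal, no diagnosis term | Portal, with diagnosis | Text, without → with | Clinician, without → with |
|---|---|---|---|---|
| 30 / 30 / 2 | 1.02 | 1.02 | 1.02 → 1.02 | 0.97 → 0.97 |
| 30 / 20 / 2 | 1.08 | 1.00 | 0.98 → 0.98 | 1.01 → 1.01 |
| 50 / 20 / 2 | 1.20 | 0.97 | 0.95 → 0.95 | 0.96 → 0.96 |
| 50 / 20 / 3 | 1.44 | 1.03 | 1.00 → 1.02 | 1.03 → 1.04 |

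The standard deviation of the log hazard ratio across replicates was at most 0.151 for portal and 0.233 for text and clinician. The Monte Carlo standard error is therefore at most 0.151/√60 = 0.02 and 0.233/√60 = 0.03. The portal bias is well outside that error in the two rows with a 50/20 mix. The text and clinician terms hardly move.

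**4. What a diagnosis term cannot do.** If every patient followed the same three-week schedule, 12 weekly time terms plus three nudge indicators would give 15 columns of rank 12. The nudge terms would then be fully determined by time since first contact. They are estimable only through patients who enter at text or through staggered starts, which is why the portal contrast matters.

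**The case against.** **Stratified reporting.** The Study design sentence may mean only that rates will be reported by subgroup. Its list is illustrative, and Measures plans just such reporting. This stands in part: a flat contradiction is not certain. But the reference to a time-varying covariate is modelling language, and the article leaves both readings open.

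**Diagnosis is not ignored.** It is a planned moderator and is available to the adjusted model, where race is only an example. A sparse main model followed by an adjusted one is common. This stands too, but the adjusted model does not carry the hierarchical tests.

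**Stronger readings that the article does not support.**
- *The model adjusts for site only.* It also adjusts for time in months and clusters variances by physician.
- *Later steps will look weaker because high-uptake diagnoses leave first.* The mix effect is small, and on a time-since-contact scale much of it is absorbed by the baseline hazard. The simulated text and clinician terms hardly changed.
- *Uptake differs strongly between personal and family history.* One could pair the Background's 35% and 15% to get ln(0.65)/ln(0.85) = 2.65. But the 35% is a general figure for ovarian cancer, while the 15% is a local upper bound for family history. Locally, the Background puts previous ovarian cancer and family history together as very low. Its higher local rates are for breast cancer diagnosed within two years, and those patients are outside the eligibility criteria.
- *Portal access differs by diagnosis.* Nothing in the article says so.

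**Conclusion.** The point holds as a mismatch between two descriptions of the primary analysis, and as an avoidable exposure to confounding in one contrast. The primary model omits a baseline variable that the outcome description names beside clinic and that is already in hand for every patient.

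The possible bias falls on the portal versus no-portal contrast. It is zero if diagnosis mix is equal across portal access. It gave spurious portal hazard ratios of 1.08, 1.20 and 1.44 under the three assumed unequal mixes, and would go below 1 if the mix were reversed. The mix, the prognostic strength of diagnosis and the share without an account are all assumptions, so neither size nor direction can be stated for this study. Depletion between steps is a minor matter, at most about 10% over the range tried. The case for changing the model rests on its low cost and on settling the choice before the data are seen, not on a demonstrated large bias.

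**What to change.** In Sample size, power, and statistical analysis, add eligibility diagnosis group to the primary Cox model as a stratum or fixed effect, and keep the site term as it is. Use three broad groups: personal ovarian cancer, personal breast cancer (early-onset or triple-negative), and unaffected with a family history. The family-history criteria apply to unaffected people only, so the overlap to settle is between the ovarian and breast groups. State in advance to which group a patient with both belongs. Leave the remaining EHR covariates in the adjusted model. If the authors intend diagnosis only as a reporting subgroup, the Study design sentence should say so.

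The cost is one line of analysis text and one allocation rule, with no new data. The drawback is that one or two strata may be small; a fixed effect avoids splitting the risk sets. The change does not resolve the near-collinearity of the nudge terms with time since first contact, which needs its own treatment.

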### Study setting, population, and duration

This study will be conducted at gynecologic practices within two Penn Medicine centers: Penn Health for Women Radnor and the Helen O. Dickens Center for Women. These sites serve substantially different patient populations in terms of racial identity and insurance coverage, which may affect testing uptake. Most patients at Radnor are white (83.7% white, 6.5% Black, 3.0% Asian, 6.8% other/unknown), while the Dickens Center predominantly serves Black patients (73.7% Black, 18.9% white, 2.1% Asian, 5.3% other/unknown). Patients seen at these two sites since January 1, 2009 will be selected by an EHR-based algorithm established previously [71] using the following eligibility criteria: (1) serous ovarian cancer diagnosed more than two years prior to study contact; (2) breast cancer diagnosed at under 50 years of age more than two years prior to study contact; (3) triple-negative breast cancer diagnosed at any age more than two years prior to study contact; (4) unaffected individuals reporting a family history of ovarian cancer; (5) unaffected individuals reporting a family history of male breast cancer; and (6) at least two Penn Medicine appointments within the last three years. Utilizing electronic phenotyping in the EHR, participants who have previously received genetic counseling and testing will be excluded. Approximately, 3000 patients at these sites have been identified as eligible for genetic testing for familial high-risk breast and ovarian cancer based on these criteria, and these patients make up the target sample. The clinician sample (*N* = 30) will consist of gynecologists at participating practice sites associated with these patients. It is anticipated that the study will take approximately 18 months to complete. The study was approved by the University of Pennsylvania Institutional Review Board. The trial presents minimal risks to participants, and a waiver of informed consent was approved for all study aims.

### Overview of rapid-cycle approaches and study procedures

The first step to increasing genetic testing is to identify patients who might benefit from it by utilizing updated tools in the EHR. Penn Medicine’s Abramson Cancer Center Electronic Phenotyping Core developed algorithms for identifying patients based on cancer registry data and family history fields in the EHR. These electronic phenotyping procedures were used to identify randomly selected patients to include in pilot testing during the rapid cycle approaches (RCAs).

As a project led by the National Cancer Institute-funded Penn Implementation Science Center in Cancer Control (Penn ISC3; P50CA244690), this study builds on strategies from the center’s prior research [74, 75]. As in prior studies, RCAs to quickly learn and innovate from pilot tests [41, 76–78] were used to de-risk and optimize our nudges as implementation strategies. They also helped us refine our methods based on relevant experiences from clinicians and patient partners to maximize their effect and study efficiency. This work is summarized in Table 1. RCAs involved advisory meetings with experts in behavioral economics, discussions with patient and family partners on the Basser Young Leadership Council, and meetings with clinicians with expertise in breast and ovarian cancer genetic testing. In addition, given the calls to incorporate implementation science and health equity together in genomic medicine [43, 79], experts at integrating these fields provided guidance on study design and message content. We then designed prototype messages and received feedback about content and delivery mechanisms. Finally, two template patient nudges were pilot-tested by randomizing 200 patients to one of two messages that were based on different heuristics. After patients were sent their arm’s respective pilot message via the patient portal and text message, the proportions of patients who engaged with messages, contacted the CREP scheduling staff and scheduled a genetic counseling appointment were assessed. Based on extensive review from partners and pilot test results, the nudges to be implemented in the overall study were designed as follows.

**Table 1 Tab1:** Rapid cycle approaches to develop, de-risk, and optimize implementation strategies

Domain	Initial approach	Iterative work	Output
Clinician nudge	Best practice alert (BPA) with pended order for genetics counseling Key questions: • What is the best timing and mechanism for sending clinician nudges, since eligible patients won’t be in the clinic very often? • What are the key cognitive heuristics affecting genetic testing ordering?	Method: Meetings with experts in behavioral science, implementation science, health equity, and informatics; discussions with clinicians Key feedback: • Alert fatigue can cause annoyance for care team members • Clinicians preferred a pre-selected recommendation which can be signed efficiently • Status quo bias was a key barrier	“Pend and send” default order for genetic testing with accountable justification for clinicians who decline the order
Patient nudge	Sequential nudges delivered via the patient portal and text message Key questions: • What strategies can be used to overcome inequities in patient portal access? • What are the key cognitive heuristics affecting genetic testing uptake?	Method: Meetings with experts in behavioral science, implementation science and health equity; patient review; pilot tests which contacted 200 patients via the patient portal and text message with two potential nudges Key feedback: • Messages with a clear call to action up front can spur behavior change • Wording changes to increase readability would be valuable • Pilot tests revealed that the message emphasizing ease led to high engagement	Patient portal messages emphasizing ease and text messages emphasizing the importance of taking action to prevent cancer

### Patient nudges (patient portal and text message)

The patient-directed strategies will be delivered via two mechanisms: the patient portal and text message. Figure 2 shows both patient-directed nudges. The content of the nudges was influenced by past research documenting that patients tend to focus on the potential adverse effects of action vs. inaction [52, 53, 80] and was reviewed and modified by a group of clinicians and patient partners. Eligible patients will initially be contacted via the patient portal. This “low-touch” implementation strategy can provide information about the impact of using patient health system portals to encourage the uptake of genetic testing. If patients do not respond, or if they are identified as not having a patient portal account, they will be moved to the second implementation sequence. In this sequence, patients will be sent text messages using similar content from the first sequence, encouraging them to sign up for genetic counseling appointments. Patients who do not respond to the first two nudges will be identified for the clinician's nudge.

**Fig. 2 Fig2:**
[figure not shown]
Patient nudges

### Clinician nudge

Our preliminary formative work involved the development of prototype messages to integrate as nudges delivered to clinicians through the EHR. As with the patient nudge, we created multiple versions of the nudges and ascertained feedback from partners about the message content and design, as well as the method and timing of delivery. Also, the study team engaged with research from another study promoting genetic testing and adapted the wording and format of a clinician nudge to design a message considered most likely to receive clinician support.

Both study sites use Epic (Epic Systems Corporation, Verona, WI) to deliver care. Recent upgrades to Penn’s Epic instance introduced the “pend and send” capability. Using this process, the research team will create a pended order for a genetics consult for eligible patients who did not respond to prior patient-directed strategies. As detailed in Fig. 3, the clinician nudge will include text leveraging status quo bias, a default order for a genetics consult, and a requirement for clinicians to provide accountable justification if they decline the order. Clinicians can efficiently sign orders in the InBasket without needing to open each encounter separately. The consults are then routed directly to the CREP scheduling team, who will contact the patient to schedule an appointment with a genetic counselor. We pilot-tested the “pend and send” mechanism in the RCAs. Clinicians have been engaged at both clinics so that they are aware of this initiative and clinician education has been provided.

**Fig. 3 Fig3:**
[figure not shown]
Clinician nudge

### Measures

The primary outcomes are the rates of contacted patients who schedule and complete a genetic counseling appointment within six months after each sequential step, collected via the EHR. As process measures, we will evaluate the proportion of patients who open MPM messages or respond to text messages within one month of receiving them, as well as the proportion of pended orders that clinicians sign within one month to refer patients for a genetics consult. Potential moderating variables will also be collected, including patient demographics (age, race, ethnicity, diagnosis, health insurance, address, and geocoded area as a proxy for neighborhood-level socioeconomic status), clinician data (practice site, years in practice), and practice-level information (community vs. hospital-based setting, urban vs. non-urban location, health insurance mix). These data will be used to describe the sample of participating patients and clinicians and to identify factors that may influence strategy effectiveness. Genetic counseling and testing rates will be evaluated after being stratified by these factors.

